### Sample size

Sixteen pairs of premises provide 80% power to detect a 0.8 standard deviation difference in premises-level rates of intoxication and violence using a two-tailed alpha of 0.05. The study was an exploratory trial and a significant effect was not anticipated.

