### Matching

The unit of allocation was the individual licensed premises, stratified by risk of harm and area. A risk index was calculated for each licensed premises using the formula Risk = P/(T*C) where P is the number of police recorded incidents in the twelve months preceding project start, T is the number of hours open after 11 pm on Friday and Saturday night and C is the maximum premises capacity. Matching was incorporated into the study to reduce possible imbalances between treatment arms expected with a small sample size, but was not accounted for in subsequent analyses due to the loss of degrees of freedom [18].

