### Randomisation

The exploratory trial was a two-armed parallel cluster randomised trial in which premises was the unit of randomisation. Only once the audits and action plans for all thirty-two premises had been completed did randomisation take place. Each premises in a pair was assigned the number one or two in the order they were recruited by Researcher 1. Independently a random number was generated and relayed by telephone to Researcher 1. If an odd number was generated, the premises identity marked one was placed in an envelope and sealed. If an even number was generated, the premises identity marked two was placed in an envelope and sealed. Unselected premises names were placed out of sight. Researcher 1 left the randomisation room and was replaced by Researcher 2. A random number was independently generated and relayed by telephone to Researcher 2. If an odd number was generated, the premises identity in the envelope was allocated to the control group. If an even number was generated, the premises identity marked was allocated to the intervention group. Each premises had a 50% chance of being in either control or intervention group.

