### Statistical analyses

In the available ED and police data concerning violence, it is not possible to determine whether multiple incidents on the same day are related or not: it is feasible that a single episode involving violence can lead to multiple arrests and/or injuries requiring hospital treatment. Furthermore, as the primary interest is premises-level risks it is reasonable to assume that premises failings persist across a session and therefore that multiple incidents in one session can be assumed as partly reflecting those risks. For violence, therefore, we assumed that one or more violent incidents indicated that for that session the premises was in a state of failure and was thus coded as a binary event. Furthermore, it is likely that any intervention effect will wane over time, particularly as premises are usually subject to high staff turnover rates. Moreover, for any definitive trial it is feasible that numerous external factors might influence premises-level failure rates, such as sporting events and temporary closure. While Poisson models can accommodate aggregate count data and would normally be suitable, in order to account for potential intervention wane, time varying covariates, censoring, multiple events and discontinuous risk intervals, the preferred approach was to develop an Andersen-Gill model [21], a derivation of the Cox proportional hazards model [22,23]. The individual level BrAC data are clustered in premises and location and is available pre- and post-intervention. This suggests that a multilevel mixed-effects linear regression [24] is appropriate from which design effects and intra-cluster correlation coefficients for BrAC and the other survey measures can be calculated.

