### Sample, stratification and matching

Thirty-two premises were recruited for participation in the study (Town A: 6; Town B: 10; Town C: 8; Town D: 6; Town E: 2). Data used in calculating the risk index were generated acquired by accessing premises licences (publicly available through local council offices) and in consultation with premises representatives. Within towns, premises were matched by estimated risk score.

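### The Sample size section claims 80% power for 0.8 SD from sixteen pairs, but the Matching section drops the pairing; a simple unmatched comparison of 16 v 16 premises has about 59–62%

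*Protocol article*

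**What the plan says.** The Sample size section of the protocol article reads "Sixteen pairs of premises provide 80% power to detect a 0.8 standard deviation difference in premises-level rates of intoxication and violence". The significance level is 5%, two-sided. The section adds that the trial is exploratory and that no significant effect was expected. It does not say whether the 0.8 is in between-premises SDs or in SDs of within-pair differences, and it names no test and no correlation.

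The Matching section explains that premises were matched to limit imbalance in a small sample. Of the matching it then says: "but was not accounted for in subsequent analyses due to the loss of degrees of freedom".

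Under Statistical analyses, for violence, "the preferred approach was to develop an Andersen-Gill model". For breath alcohol concentration, a multilevel linear regression on pre- and post-intervention data is proposed. Neither model is described with a term for the pair. Under Sample, stratification and matching: "Thirty-two premises were recruited for participation in the study", which is 16 per arm.

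**The concern.** The power claim is expressed in pairs, but the analysis described elsewhere in the same Methods section ignores the pairs. If the pairs are ignored, the comparison is of 16 premises with 16 premises, and a 0.8 SD difference is not detected with 80% power by any simple unmatched test.

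This matters because the article's Objective says that the study should supply design parameters for a possible large effectiveness trial. A planner who took 16 pairs, 0.8 SD and 80% as a consistent set, and then planned an unmatched trial, would start from a figure that the unmatched design does not deliver. The Stratification part of the Discussion expects matching to matter less as samples grow, so an unmatched successor is plausible.

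**Working it through.** **Inputs, all from the article.** 16 pairs (32 premises, 16 per arm); difference d = 0.8 SD in premises-level rates; two-sided alpha 0.05; target power 80%. Within-pair correlation, baseline correlation and the type of SD are not stated, so ranges are shown.

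**1. Can the stated figure be reproduced with the pairing?** Paired t-test, 15 df.

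- Reading 0.8 as SDs of the within-pair difference: noncentrality = 0.8 × √16 = 3.2, power 84.8%. Fifteen pairs already give 80%, and 16 pairs detect 0.749 SD with 80% power. On this reading the claim holds as a floor.
- Reading 0.8 as between-premises SDs: the SD of a within-pair difference is √(2(1 − ρ)), so noncentrality = 3.2 / √(2(1 − ρ)).

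| Within-pair correlation ρ (assumed) | Paired power |
|---|---|
| 0 | 56% |
| 0.3 | 72% |
| 0.43 | 80% |
| 0.5 | 85% |

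**2. Without the pairing.** Two-sample comparison, 16 per arm, unadjusted.

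- Noncentrality = 0.8 × √(16/2) = 2.263.
- Normal approximation: Φ(2.263 − 1.960) = Φ(0.303) = 61.9%.
- t-test, 30 df: 59.1%.
- One-sided versions do not reach 80% either: 71.4% (t) and 73.2% (normal).
- Difference detectable with 80% power: (1.960 + 0.842) × √(2/16) = 0.99 SD (normal), or 1.02 SD (t).
- Premises per arm for 80% at 0.8 SD: 2 × (2.802/0.8)² = 24.5, so 25 (normal), or 26 (t), which is 52 premises in all.

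**3. Unmatched test applied to data that really are pair-correlated.** The 59.1% treats the arms as independent. In 200,000 simulated trials per setting, with ρ from 0.35 to 0.5, the unmatched t-test had 61.1% to 62.4% power, and its type I error fell to between 1.7% and 0.8%. The range of 59–62% therefore covers both assumptions.

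**4. Unmatched but adjusted for a baseline value.** With premises-level baseline correlation r (assumed), the effective difference is 0.8 / √(1 − r²). Power by t is 63% at r = 0.3, 67% at 0.4, 72% at 0.5 and 78% at 0.6. For 80%, 0.8 / √(1 − R²) must equal 1.024, so R² = 1 − (0.8/1.024)² = 0.39, or about 0.4.

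**5. Cost of keeping the pairs.** The reason given for dropping them is lost degrees of freedom (30 to 15). If the pairing carries no information (ρ = 0), this costs about 3 points (59.1% to 56.2%). At ρ = 0.35 the paired test has 75% and the unmatched test 61%.

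**The case against.** Several points can fairly be made for the article.

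- **The figure is not a miscalculation.** On one natural reading of the SD, sixteen pairs more than meet 80%. This stands: the defect is an inconsistency between two sections together with an undefined SD, not faulty arithmetic.
- **No two-sample t-test is planned.** A reader might infer that the planned analysis has 59% power. The article does not support that. The named models are an Andersen-Gill model on session-level events and a multilevel model on individual breath readings, and the article gives no event rate, number of sessions, intra-cluster correlation or cluster size from which their power could be worked out.
- **Matching is not the only route to 80%.** A reader might infer that 80% can come from a matched-pair analysis alone. Step 4 shows that a strong enough baseline or covariate adjustment would also do it. Baseline measures are collected, but no such adjustment is tied to the power claim and no correlation is given.
- **The trial is exploratory.** The article expects no significant effect, says effect sizes are unknown, and looks to intra-cluster correlations and design effects as outputs. A reader might infer that 0.8 SD and sixteen pairs are being carried into a definitive-trial calculation, or that a null result will be taken to exclude 0.8 SD. The article does neither. This lowers the consequence but does not make the stated power agree with the stated use of the matching.
- **A condensed article may leave inputs to the full protocol.** That excuses the missing correlation taken alone. It does not excuse two printed statements that conflict.

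**Conclusion.** The point holds as an inconsistency between the Sample size and Matching sections. Eighty per cent power at 0.8 SD depends on the pairing, or on an adjustment that is not stated, while the article says that the pairing was not used. A simple unmatched, unadjusted premises-level comparison of 16 v 16 falls about 18 to 21 points short of the claim (59–62% against 80%); its detectable difference at 80% power is about 1.0 SD, not 0.8.

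These figures assume roughly normal premises-level rates, equal variances, no loss of premises and, for the unmatched benchmark, 0.8 in between-premises SDs. They do not describe the power of the named models, which stays unknown. Severity is moderate: the sample is already fixed, and the trial was not set up to show a significant effect.

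**What to change.** Choose one of two restatements.

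1. **Keep the matching out of the analysis.** Reword the Sample size section to say that a simple unmatched comparison of 16 v 16 premises has about 59–62% power for 0.8 SD and 80% power for about 1.0 SD. Label this as a benchmark and not as the power of the Andersen-Gill or multilevel model, so that no new mismatch is created.
2. **Keep 80% at 0.8 SD.** State which SD is meant, the test, and the assumed within-pair correlation (about 0.43 if the SD is between premises) or R-squared (about 0.4). Revise the Matching section so that the analysis uses the pairing, the matching factors (area and risk index) or the baseline value.

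Both options change wording and need no extra premises. The first prints a less favourable figure. The second commits the analysis to a pair term or covariates, at the small cost in degrees of freedom shown in step 5 if the pairing is used and proves uninformative.

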### Process evaluation

A detailed process evaluation is being undertaken within the RCT evaluation. The project employs a framework described by Steckler and Linnan [25] to explore the implementation, fidelity and acceptability of the intervention. The aims of this process evaluation are twofold: first, to identify and explore views on appropriate and acceptable approaches to prevention across a range of stakeholders and, second, to determine how the intervention was implemented. In the former, local and national stakeholders involved in NTE governance, the sale of alcohol and the prevention of alcohol-related harm and disorder will be interviewed to identify obstacles, facilitators and acceptability of premises-level interventions. Results will inform the development of appropriate structures, resources and partnerships for any definitive trial. The latter component assessing intervention implementation and fidelity and any control arm contamination will allow the intervention to be refined for future iterations of the project and will facilitate the interpretation of outcome effects. An overview of the process evaluation plan is shown in Table 2.

**Table 2 T2:** Description of the process evaluation

Group	Process Point & Method	Aims
Stakeholders in the NTE with respect to: • the governance of the NTE • the sale of alcohol • the prevention of alcohol related harm and disorder	Pre-intervention Semi-structured interview	• Views on intervention approaches and acceptability
Bar staff from premises in the study areas - not necessarily premises in the study	Pre-intervention Semi-structured interview	• Views on intervention approaches and acceptability
Premises Auditors/Street Surveyors	Post-intervention Focus Group	• Street survey protocols for future trials
Premises representative* (Intervention arm)	Post-intervention Semi-structured interview	• Views on intervention theory and acceptability • Contextual influences on implementation • Fidelity to action plans
Premises representative^1 ^(Control arm)	Post-intervention Semi-structured interview	• Assess contamination within double blind design

* Usually the Premises manager

## Results

### Recruitment

#### Phase 1: Letter of invitation

Recruitment through letters of invitation to all premises' Designated Premises Supervisors (DPS) in study areas produced low levels of interest: 1.5% of all premises' DPSs written to responded favourably.

#### Phase 2: Premises managers forum

Recruitment through presentation at fora where premises staff were present produced marginally higher rates of interest compared to written invitations yielding an estimated success rate of 6.2%.

#### Phase 3: Premises recruited with police

Recruitment through premises visits in the company of a police officer yielded a success rate of 100%.

#### Phase 4: Premises recruitment, no police

Recruiting through premises visits by a researcher who had been introduced to the premises by a police officer, but who did not attend with the researcher, yielded a success rate 100%.

### Sample, stratification and matching

Thirty-two premises were recruited for participation in the study (Town A: 6; Town B: 10; Town C: 8; Town D: 6; Town E: 2). Data used in calculating the risk index were generated acquired by accessing premises licences (publicly available through local council offices) and in consultation with premises representatives. Within towns, premises were matched by estimated risk score.

## Discussion

### Key issues in conducting the evaluation

#### Recruitment

in order to determine those resources required to recruit premises into a trial, recruitment methods of varying intensity were piloted. At the lowest intensity, premises were approached without reference to external agencies such as the police. This method did not yield a response rate sufficient for any future trial, suggesting that the problem premises cannot be relied on to voluntarily address alcohol-related harm. The only feasible recruitment method for a future trial would require the support of the police.

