### Recruitment

As the characteristics of NTEs and the violence prevention resources available can vary considerably across jurisdictions, the study team implemented the intervention across five towns (reduced to four areas for analytical purposes as two towns, D and E in Table 1, are in close proximity and are typically referred to as an homogenous region). The four areas covered by the study were selected as they featured NTE types representative of those in England and Wales, including cities and small to medium-sized towns.

**Table 1 T1:** Recruited premises by recruitment intensity

Recruitment Strategy	Town A	Town B	Town F	Town D	Town E	Town C
Resident population	325,000	227,000	50,000	47,000	35,600	37,000
**Number of eligible licensed premises**	**89**	**81**	**30**	**11**	**9**	**10**
**Invitation letters sent**	89	81	30	26		
**Expression of interest**	4	2	1	1		
**Recruited**	2	1				

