**Premises managers forum**						
**Number of eligible licensed premises**	30	25	10			
**Expression of interest**	2	3				
**Recruited**	1	3				

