**Premises visits, no police**						
**Number of premises targeted**	2	7		6	2	2
**Recruited**	2	7		6	2	2

A variety of recruitment strategies that varied in intensity were piloted in phases across the intervention areas. Local police in each area were aware of and supportive of the project. However, they were not involved either in the design or evaluation of the intervention. While it was desirable that police involvement be kept to a minimum in order to facilitate transparency, it was concluded that local police licensing officers represent the most efficient route for accessing and recruiting licensed premises managers. Therefore, licensing officers were involved in the recruitment methodology. Premises were first invited to participate by letter, following which researchers made appeals at premises manager meetings. Once these first two options were exhausted, visits to premises were made by Project staff. All visits involved police officers, either directly through accompanying researchers or indirectly through officers introducing the study to premises staff beforehand. This order was maintained where possible, however due to the timing of some local meetings, the availability of premises staff and Project time constraints, it was not possible to follow this order of events strictly in each area. Irrespective of a premises pathway into the study all premises were visited by a member of the research team before the study commenced in order to describe the project in detail, to allow representatives to ask questions, and to gain verbal consent. Each premises representative was given a detailed description of the trial and what would be required of them.

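### The pilot did not test a recruitment visit without police, so it cannot show that police support is the only feasible route; the letter yield and two town counts also need correcting

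*Protocol article*

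**What the plan says.** Comparing recruitment methods is a stated objective of the exploratory trial (Abstract, Objective). Four strategies were piloted: invitation letters, appeals at managers' forums, visits with a police officer present, and visits that Table 1 and the Phase 4 heading label as having no police. The Methods text on recruitment then says: "All visits involved police officers, either directly through accompanying researchers or indirectly through officers introducing the study to premises staff beforehand". The Phase 4 paragraph itself confirms that an officer had introduced the researcher. The Discussion concludes: "The only feasible recruitment method for a future trial would require the support of the police".

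On yields, the Phase 1 result is that "1.5% of all premises' DPSs written to responded favourably". The Phase 2 result describes the forum presentations as "yielding an estimated success rate of 6.2" per cent. Both visit strategies are reported at 100%.

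The section on sample, stratification and matching gives the premises recruited as "Town A: 6; Town B: 10; Town C: 8; Town D: 6; Town E: 2", 32 in all, with matching done within towns.

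**The concern.** To say that police support is required, one needs some idea of how an otherwise similar approach does without it. Here the low-yield strategies were letters and forum appeals with no stated police role, and the high-yield strategies were visits to the premises, all with one. The visit and the police role came together. The no-police label hides this: from Table 1 alone a reader would think that visits without police had been tried and had succeeded every time, which would contradict the Discussion.

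The question matters for the definitive trial. The article itself says that it was desirable to keep police involvement low for the sake of transparency, so whether police are truly needed is a live design question. The yields by method will also feed that trial's recruitment plan, so each rate should mean what its sentence says.

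**Working it through.** **Step 1. What was tried.** From Table 1, the Methods text on recruitment, and Phases 1 to 4 of the Results:

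| Approach | Police role | Denominator | Recruited |
|---|---|---|---|
| Letter | none stated | 226 letters sent | 3 |
| Forum appeal | none stated | 65 eligible premises | 4 |
| Visit, officer present | direct | 6 targeted (Town C) | 6 |
| Visit after police introduction | indirect | 19 targeted | 19 |
| Visit without police | none | 0 tried | not estimable |

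The recruits add up: 3 + 4 + 6 + 19 = 32. Letters and forums supplied 7 of 32 (22%), and police-supported visits 25 of 32. The last row is empty, so the data hold no contrast between a visit with and a visit without police. The strategies were also applied mostly in sequence, visits last, and the visit denominators count premises targeted, not all those eligible.

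**Step 2. The letter yield.** Inputs from Table 1: "Invitation letters sent 89 81 30 26" and "Expression of interest 4 2 1 1", with 2 and 1 recruited.

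- Letters: 89 + 81 + 30 + 26 = 226. Interest: 4 + 2 + 1 + 1 = 8. Recruited: 2 + 1 = 3.
- The article's figure: 3 recruited / (89 + 81 + 30) = 3/200 = 1.5%. This is recruitment in Towns A, B and F.
- As the sentence defines it (favourable responses among all written to): 8/226 = 3.5%.
- Recruited among all written to: 3/226 = 1.3%.

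So 1.5% can be obtained from Table 1, but its numerator is recruits rather than favourable responses, and its denominator leaves out 26 letters.

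**Step 3. The forum yield.** Inputs from Table 1: "Number of eligible licensed premises 30 25 10", interest 2 + 3 = 5, recruited 1 + 3 = 4.

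- Eligible: 30 + 25 + 10 = 65.
- Recruited: 4/65 = 6.2%, the article's figure.
- Interest: 5/65 = 7.7%.

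In Towns A, B and F letters sent equal eligible premises (89, 81 and 30). The 1.5% and the 6.2% are therefore the same kind of quantity: recruits over eligible premises in those towns.

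**Step 4. Town counts.** Adding the recruited rows of Table 1 by column, in the order letter, forum, accompanied visit, introduced visit:

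| Town | Table 1 | Text |
|---|---|---|
| A | 2 + 1 + 0 + 2 = 5 | 6 |
| B | 1 + 3 + 0 + 7 = 11 | 10 |
| C | 0 + 0 + 6 + 2 = 8 | 8 |
| D | 0 + 0 + 0 + 6 = 6 | 6 |
| E | 0 + 0 + 0 + 2 = 2 | 2 |
| Total | 32 | 32 |

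Towns C, D and E agree and A + B = 16 both ways, so one premises is assigned to different towns.

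**The case against.** The strongest reply is that the practical inference survives. Whichever definition is used, letters gave 1.3% to 3.5% and forums 6.2% to 7.7%, and of the methods piloted only police-supported visits recruited enough premises. That stands, and it is what the conclusion should say. The police role is also disclosed: the Methods text and the Phase 4 paragraph state it plainly. The label is poor, but the information is there. The Abstract's conclusion is already hedged, since it suggests recruiting with police assistance and does not claim necessity.

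Several stronger readings are tempting, and the document does not support them:

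- *That letter and forum premises had no personal contact.* Forums were in-person appeals, and all premises had a visit from the research team before the study began, to explain it and obtain verbal consent. The untested case is narrower: a recruitment visit to the premises with no police role.
- *That 1.5% cannot be reproduced, or that letter and forum rates use different metrics.* Steps 2 and 3 show otherwise. The fault lies in how the sentence defines the figure.
- *That matching failed because 5 and 11 are odd.* The counts in the matching section are all even and can be paired. The mismatch shows only that Table 1 and the text disagree.
- *That police recruitment biases the outcome because police also supply outcome data.* The article says that police took no part in design or evaluation, and randomisation came after audits and action plans for all 32 premises were complete, so the recruitment route could not depend on arm.

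**Conclusion.** The point holds in limited form. The word only in the Discussion goes beyond what was compared: 25 of 25 targeted premises were recruited by visits with police present or after a police introduction, and no visit without either was tried. The pilot leaves open whether police are needed. It does not show that they are unnecessary, and recommending police-assisted recruitment remains reasonable.

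The Phase 1 figure is wrong as defined: 3.5% against the stated 1.5% for favourable responses, or 1.3% for recruits among all letters. One premises is counted in different towns by Table 1 and the text.

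The exact 95% interval for 25/25 is 86% to 100%, but it treats the premises as independent draws from a defined population. They were targeted, not randomly chosen, and all accompanied visits were in one town, so the interval should not go into the conclusion.

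The arithmetic assumes that the Table 1 entries sit in the columns in which they appear. The letter and forum totals do not depend on this; the three-town match for 1.5% and the town sums do. The exact agreement for Towns C, D and E makes a layout error an unlikely explanation of the mismatch.

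**What to change.** 1. Discussion, Recruitment: replace the last sentence with wording such as: of the methods piloted, only visits with police accompaniment or a prior police introduction recruited enough premises; visits without police were not tested. The Abstract's conclusion can stay largely as it is.
2. Table 1 and the Phase 4 heading: rename the fourth strategy as a visit after police introduction.
3. Results, Phase 1: replace 1.5% with 8/226 (3.5%) interested and 3/226 (1.3%) recruited. Phase 2: give 5/65 (7.7%) interested and 4/65 (6.2%) recruited, so that both phases show the same two rates with their denominators.
4. Reconcile the Town A and Town B counts in Table 1 and in the section on sample, stratification and matching against the list of matched pairs.

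The cost is a few sentences, one label and a check of one list. The price is a more modest conclusion on recruitment; nothing in the design, the sample size or the outcome analysis changes.
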